**Methods:**

Guided by human-centred design approach, the implementation of this study will be divided into two phases: development of intervention, and implementing and testing feasibility. The service-delivery intervention will be co-created along with relevant stakeholders and informed by contextual evidence that is generated through formative research. It will include capacity-building of maternity teams, and the improvement of governance and accountability mechanisms within public health facilities. The technical content will be primarily based on WHO’s intrapartum care guidelines and mental health Gap Action Programme (mhGAP) materials. A mixed-method, pre-post design will be used for feasibility assessment. The intervention will be implemented at six secondary-level healthcare facilities in two districts of southern Sindh, Pakistan. Data from multiple sources will be collected before, during and after the implementation of the intervention. We will assess the coverage of the intervention, challenges faced, and changes in maternity teams’ understanding and attitude towards SDMC. Additionally, women’s maternity experiences and psycho-social well-being—will inform the success of the intervention.

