### Intervention

It will be a theory-driven, inclusive service-delivery package which will be developed using the principles of the human-centred design approach. The model will include capacity-building of maternity teams, and the improvement of governance and accountability mechanisms within public health facilities to ensure that all women are treated with compassion and dignity, while also catering for their diverse needs, including disabilities and common mental health conditions. The integration of psychosocial support in routine maternity care will be a unique feature of the intervention package, a principal aim of which is to address the psychological needs of birthing women and their companions. The technical content of the SDMC training handbook will be based on two integrated modules: WHO’s intrapartum care guidelines [14] and Mental Health Gap Action Programme (mhGAP) training [26] and implementation guidelines [27]. As part of the SDMC package, maternity staff will have job-aids for referencing of essential SDMC behaviours, steps of providing psychosocial support, and reassuring maternity patients about their rights and responsibilities.

Operationally, the core components of intervention would include: capacity-building of a typical maternity team comprising clinical staff (gynaecologists, doctors, nurses) and support staff (ward boys/porters and maids); collaborative care, a team-driven approach, led by gynaecologists (ward in-charge), attempts to integrate care and behaviour practices of staff according to the principles of measurement-guided care-plans, quality improvement and accountability, with a focus on meeting SDMC needs; staff and patient feedback: a complaints register will be maintained by designated staff; and brief exit interviews will elicit, and record, the degree to which care has been supportive and respectful; Accountability and governance (performance review): reports of non-respectful care will be discussed, and remedial actions decided, in periodic meetings.

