#### Women’s experiences

*Quantitative methods*. Pre-post intervention assessments will gather information on women’s experiences of SDMC at health facilities, and suffering of postpartum depression within 42 days of childbirth. Unlike health system assessment, two independent group of women will be enrolled in baseline and endline. Recently published structured questionnaire on mistreatment during childbirth will be contextually adapted and used for these pre-post assessments [33]. Postpartum depression and anxiety will be assesed using Patient Health Questionnaire– 9 and Generalised Anxiety Disorder– 7, respectively.

*Sample size calculation*. In order to get a sense of sample size requirement for a meaningful change study outcomes, the sample size was estimated with varied effect sizes. Mean score mistreatment was considered as key outcomes which is taken from a background study in similar setting that yielded a mean score of 25 (score range 0 to 40). A total of 308 postpartum women will be required to detect a statistical difference of 2.5-units decrease (or 10% reduction) in the mean score of mistreatment (from 25 [34] to 22.5) with standard deviation of 6 [34], 90% power, 5% level of significance, 2 design effect, and 10% lost-to-follow-up (LTFU) and/or non-response. We decided to proceed with a sample of 308 as it gives sufficient precision to perform range of additional analysis such as estimation of prevalence of different types of mistreatment and the effect of intervention on each of these types of mistreatment, while will not negatively affecting study timelines.

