*Sampling strategy*. A convenience sampling technique will be used for the selection of study participants. All women giving births at the selected hospitals during the data collection period will be invited to participate in the survey, until the desired sample is achieved. The volume of women attending each health facility for childbirth may vary; hence based on historical trends the sample size will be proportionally distributed across health facilities according to the caseload. During the consent process, participants will be informed and asked whether they would be interested in participating in a follow-up interview in their homes at six weeks of postpartum. Women who showed interest in home-based interview and gave consent will be recruited in the survey. Participants who lived outside of the study district or even in hard-to-reach rural areas of the district will be excluded from this sample due to logistical constraints.

*Data collection and management*. Standardised and contextually-adapted tools will be used in this study. All data collection tools will be translated in the relevant local language and pre-tested in similar settings prior to being used. Data collectors with prior experience will be hired and trained for baseline and endline assessments, and routine audits. In-depth interviews (IDIs) and focus group discussions (FGDs) will be conducted by trained sociologist and/or anthropologist. All data collectors will receive a comprehensive and standardised training on both theoretical and practical aspect of study instruments. In addition, data collectors will be trained on rapport building, research ethics, and interviewing techniques. Research Officer will conduct: shadow interviews (observation of data collection) and independent re-interview/assessment with a sub-sample to ensure data quality.

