For the qualitative enquires of formative research, we will use bottle-neck analysis approach to identify prevalent issues that impedes provision of SDMC in health facilities, and also determine the opportunties that can be leverage to promote SDMC. These findings will inform the development of intervention package. The qualitative data to be collected post-intervention, will be analysed to understand feasibility and acceptability of SDMC intervention, and related barriers and facilitators of implementation. We will also analyse suggestions of study participants to make improvements in the intervention package.

The researchers will thoroughly review all of the transcripts several times to identify predetermined and emerging themes from the data as per the objectives. Audio-recording of the IDIs will be transcribed verbatim and translated from Urdu/local language into English. These transcripts will be used for detailed analysis. The data will be coded and thematically analysed using QSR NVivo 11 software for Windows.

*Covariates*. The adjustment for potential confounders will be primarily required to see changes in women’s experiences of SDMC. The analysis will be adjusted for following covariates: women’s age, ethnicity, level of education, employment status, level of empowerment, socio-economic status, functional disability, and anxiety or depression. These characteristics have found to be associated with disrespectful and abusive care at health facilities [5].

The progress and success of this early-phase research will be monitored and evaluated based on key indicators presented in Table 1. The immediate outputs will be development of a training manual for health facility staff and their training which will lead to improved knowledge and positive attitude towards regarding SDMC. Simultaneously, changes in the routine system will take place to create opportunities and encourage them to practice new behaviours. Post-intervention, perceived feasibility, penetration and challenges will be assessed that inform success of the intervention.

**Table 1 pone.0263635.t001:** List of input, process, intermediary and outcome indicators.

Level of indicator	Indicators	Instrument/ means of verification	Time	Objectives
Inputs	SDMC training handbook finalised based on the feedback of feasibility testing	Training manual	Inception phase	Objective 1
	Structural changes incorporated within health system	Systemic changes	Inception phase	Objective 1

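### The pre-post model of women's experiences adjusts for anxiety or depression, but the only measures described are taken after the birth and may be a result of the care being rated

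*Protocol article*

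**What the plan says.** All places are in the protocol article.

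- **Covariates (under Women's experiences).** The purpose is stated as follows: "The adjustment for potential confounders will be primarily required to see changes in women’s experiences of SDMC". The list gives age, ethnicity, education and employment, then "level of empowerment, socio-economic status, functional disability, and anxiety or depression". The reason given is: "These characteristics have found to be associated with disrespectful and abusive care at health facilities". No instrument or time of measurement is attached to the anxiety or depression item.
- **Women's experiences, Quantitative methods.** The surveys before and after the intervention enrol two independent groups of women. They collect experiences of care and "suffering of postpartum depression within 42 days of childbirth". On instruments the text says "Postpartum depression and anxiety will be assesed using Patient Health Questionnaire" (the 9-item version), with GAD-7 for anxiety.
- **Sampling strategy.** Women giving birth at the study hospitals are asked about "participating in a follow-up interview in their homes at six weeks of postpartum". No antenatal or pre-admission measurement is described.
- **Abstract, Methods.** Women's maternity experiences and psychosocial well-being "will inform the success of the intervention".
- **Intervention.** Psychosocial support is built into the package, "a principal aim of which is to address the psychological needs of birthing women and their companions".
- **Introduction.** Two directions are given. Poor treatment at birth may end in psychological disorder, and existing anxiety or depression makes women more liable to discriminatory care.

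**The concern.** A confounder in a before-after comparison should describe the women as they arrived for care. It should not be something that the care or the intervention could have changed. A depression or anxiety score taken up to six weeks after the birth does not meet that condition. It follows the care in time, the article names it as a possible result of poor care, and the package sets out to meet women's psychological needs.

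If such a score enters the model, the period coefficient compares baseline and endline women who have the same level of postpartum distress. Any improvement in experience that goes along with lower distress is partly taken out. The women's experience score is the only service outcome in Table 1. The Discussion names potential to improve mothers' intrapartum experiences among the grounds for going on to a cluster randomised evaluation. An estimate reduced by the choice of covariates could understate that potential.

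**Working it through.** The protocol gives no figure on this point to reproduce, so the check is a linear illustration using its planning values.

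**Inputs from the article (Sample size calculation):** change in mean mistreatment score −2.5 (25 to 22.5); SD 6.

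**Assumed, because the documents give neither:** within-round correlation ρ between the mistreatment score and a standardised distress score, 0.1 to 0.5; and a further effect d of the intervention on distress (in SD) that does not pass through experience of care, 0 to −0.3.

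**General form.** Adjusted change = unadjusted change − (within-round slope of experience on distress) × (difference in mean distress between rounds). The slope is 6ρ. The shift is zero if ρ = 0, or if mean distress is the same in both rounds.

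**Case A: distress only follows from care (d = 0).** Difference in distress = ρ × (−2.5/6). Adjusted change = −2.5 + 6ρ × ρ × 2.5/6 = −2.5(1 − ρ²).

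| ρ | Adjusted change | Share lost |
|---|---|---|
| 0.1 | −2.475 | 1% |
| 0.3 | −2.275 | 9% |
| 0.5 | −1.875 | 25% |

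**Case B: distress only precedes care, with the same mean in both rounds.** Difference in distress = 0, so the adjusted change is −2.5 at any ρ and nothing is lost.

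**Both directions, as in the Introduction.** Let b be the part of the correlation that runs from care to distress, with b between 0 and ρ, and let prior distress be equal in the two rounds. Difference in distress = b × (−2.5/6), so the share lost is 6ρ × b × (2.5/6) / 2.5 = ρb. This lies between 0 (Case B) and ρ² (Case A).

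**Case C: a further direct effect on distress.** Adjusted change = −2.5 − 6ρ × (ρ × (−2.5/6) + d).

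- ρ = 0.1, d = −0.1: −2.415 (3.4% lost).
- ρ = 0.3, d = −0.3: −2.5 + 1.8 × 0.425 = −1.735 (30.6% lost).
- ρ = 0.5, d = −0.3: −2.5 + 3 × 0.5083 = −0.975 (61% lost).

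The last case implies a total fall in distress of 0.51 SD, larger than the 2.5/6 = 0.417 SD planned for mistreatment itself.

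**The case against.** The strongest reply is that the covariate is meant as a condition the woman brings with her. The Covariates paragraph calls the items characteristics, does not name PHQ-9 or GAD-7, and gives the same rationale as the Introduction: these conditions go with worse care. Two independent convenience samples may well differ in prior mental health, and adjusting for a real difference would reduce bias. A condensed article may also omit a history item. This stands in part: that the covariate is the postpartum score is an inference, drawn because no other measure is described. It does not rescue the postpartum score, which mixes prior state with the effect of care and cannot separate them.

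A reader might infer that the estimate is pulled toward zero whenever mistreatment and distress are linked. The documents do not support that. The Introduction also gives the reverse path, and Case B shows no shift at any correlation unless distress differs between rounds. A reader might also take the 31% or 61% loss as the expected size, but both rest on an assumed direct effect of 0.3 SD for which the article gives no basis.

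The Discussion says that change in women's experiences is not the primary objective and that the study will not give robust evidence of effectiveness. This lowers the consequence. Table 1 lists neither depression nor anxiety, so their standing as outcomes rests on the Abstract and the pre-post surveys.

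**Conclusion.** The point holds in a limited form. On the measures the article describes, the plan conditions on a postpartum score that may be partly a result of the care and of the intervention. If the intervention lowers distress, directly or through better care, the adjusted change is smaller than the change in women's experiences that the model is meant to estimate. The size is not known: from nothing, to about 1% to 25% if distress only follows from care and the within-round correlation is 0.1 to 0.5. Larger losses require a further direct effect on distress to be assumed. Prior anxiety or depression may be a real confounder, but the postpartum score is not a clean measure of it. This should be fixed. It is not critical, because the affected estimate is not the study's primary objective.

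**What to change.** - Leave postpartum PHQ-9 and GAD-7 out of the main model for women's experiences. Keep all other listed covariates, including level of empowerment.
- Analyse PHQ-9 and GAD-7 as outcomes in their own pre-post models.
- Show the experience model adjusted for these scores only as a labelled sensitivity analysis.
- If prior mental health is wanted as a covariate, use a measure that refers to before this birth, and name it. If one is already collected, stating so in the Covariates paragraph settles the point.

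**Cost.** One edit to the covariate list and two extra models on data already planned. A history item, if not already collected, means a change to the questionnaire. Without such a measure, a shift between rounds in pre-existing anxiety or depression stays unadjusted in the main model.

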## Introduction

The experience of childbirth can change a woman’s life and leave lasting memories [1, 2]. Up to a third of women appraise their experience of giving birth as traumatic [3]. These psychological distresses during labour leaves them vulnerable to the care processes in health facilities such as unfamiliar personnel, medicalised procedures and other conditions [4]. Regardless of it, women around the globe, particularly in low- and middle-income countries (LMICs) are mistreated and rarely offered psychosocial support during childbirth at health facilities [5]. Such poor encounters may have adverse effects on the quality and outcome of birthing experiences, which could lead to psychological disorders [6–9], and may deter women from seeking health care in the future [10]. Additionally, range of other socio-economic (e.g. poverty) and health-related (e.g. anxiety, depression or disability) vulnerabilities predispose women to discriminatory care which may further aggravate the situation, leading to more intense sufferings [11].

Respectful Maternity Care (RMC) not only reduces the need for superfluous medical intervention but also strengthens psychosocial processes, thus improves birth outcomes and maternal well-being [4]. In the year 2014, the World Health Organisation (WHO) issued a policy statement that “every woman has the right to the highest attainable standard of health, which includes the right to dignified, respectful health care” [12]. Subsequently, they released a revised framework for quality of maternal and newborn healthcare that put special emphasis on women’s experience of care (dignity, effective community and emotional support) [13], followed by another framework to aid understanding of different forms mistreatments encountered by women during childbirth [5]. More recently, WHO released a comprehensive set of evidence-based policy recommendations to promote women’s experiences of intrapartum care [14]. These policy directives from the WHO indicate the need for integrated health services that should not only respect women’s dignity but also fulfil their emotional or psychosocial needs during maternity care [12]. This proposition presents with an opportunity to link WHO’s Mental Health Gap Action Programme (mhGAP) materials in addressing psychosocial needs of pregnant women by bringing a positive change in the maternity care settings, as per newly set WHO standards for intrapartum care [14].

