Qualitative interviews will be audio-recorded for later transcription and translation. All quantitative data will be collected electronically on tablets. The software application, developed in Epicollect5, will have built-in validation checks to minimize data collection and entry errors. All software applications will be tested prior to their use in the study. Unique IDs will be given to each study participant which will be consistent (where applicable) in across assessments for synchronisation. Data Management person, under the supervision of study Co-Investigator will be responsible to manage all data that include: timely transfer to central database, data quality through routine assessments; data confidentiality, security, back-up, and sharing while maintaining anonymity. Study Investigators will coordinate closely with research officer and data collectors to ensure timely remedial measures.

*Data analysis*. Descriptive statistics will be used to describe the characteristics of study participants such as age, level of education, socio-economic status etc. In order observed change in women’s experiences of SDMC, advanced statistical techniques will be used to estimate changes in outcome indicators (SDMC experience) by means of multivariable linear (continuous) and logistic (binary) regression models, accounting for intra-class correlation within health facilities. We will create a composite score for women’s experiences of SDMC which will treated as outcome for pre-post comparison using linear regression. Depending on distribution of the variable, we will consider dichotomising it to see pre-post intervention changes in prevalence of SDMC experiences using logistic regression. Paired t-test (for continuous) and McNemars test (for binary) will be used to observe change in knowledge and attitudes of health facility staff before and after training. Stata version 16.1 (StataCorp LP, Texas, United States) will be used for all analyses, and p-values of 0.05 will be considered statistically significant.

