	Number of participants trained on SDMC	Training reports	Inception phase	Objective 2
Intermediate outcomes	Mean score of service providers’ knowledge of SDMC	Knowledge questionnaire	Pre-post training test	Objective 2
	Mean score of service providers’ attitude towards SDMC	Attitude questionnaire	Pre-post training test	Objective 2
Implementation/ process outcomes	Penetration of SDMC across cadre (qualitative)	in-depth interview	Endline	Objective 2
	Feasibility and acceptability of SDMC package (qualitative)	in-depth interview	Endline	Objective 2
	Barriers and facilitators to implementation of SDMC (qualitative)	in-depth interview	Endline	Objective 2
Service outcomes	Mean score of women’s experiences of inclusive, supportive and dignified maternity care	Structured SDMC questionnaire	Baseline and endline	Objective 2

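### PHQ-9 and GAD-7 are collected before and after the intervention, and psychosocial well-being is said to inform success, but neither scale is evaluated as an outcome; anxiety or depression enters the analysis only as a covariate

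*Protocol article*

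**What the plan says.** All references are to the protocol article.

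- **Abstract, Methods:** women's maternity experiences and their "psycho-social well-being—will inform the success of the intervention".
- **Women's experiences, Quantitative methods:** the pre-post assessments cover experiences of care and "suffering of postpartum depression within 42 days of childbirth", in independent baseline and endline groups. The instruments are named: "Postpartum depression and anxiety will be assesed using Patient Health Questionnaire" 9, with the GAD-7 for anxiety.
- **Data analysis:** regression models will "estimate changes in outcome indicators (SDMC experience"; the parenthesis closes right after these words, so this is the only outcome named for women.
- **Covariates:** anxiety or depression is in the list of adjustment variables for the experience model. The same section sets the basis for judging the study: "The progress and success of this early-phase research will be monitored and evaluated based on key indicators presented in Table 1".
- **Table 1, Service outcomes:** one row, "Mean score of women’s experiences of inclusive, supportive and dignified maternity care". No row mentions depression, anxiety or psychosocial well-being.

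**The concern.** The document gives depression and anxiety three roles that do not fit together: a contributor to the judgement of success (Abstract), a pre-post measurement (Quantitative methods) and a confounder (Covariates). Only the last has a stated analysis.

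These measures are not peripheral. The Introduction gives psychological disorder as a possible consequence of poor care: "Such poor encounters may have adverse effects on the quality and outcome of birthing experiences, which could lead to psychological disorders". The Intervention section presents psychosocial support as a distinguishing feature of the package. Under the plan as written, the experience score could improve while depression or anxiety stayed the same or worsened, and no stated comparison would show it.

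The covariate role raises a second problem. If the adjustment uses the postpartum scores, the comparison of baseline and endline experience is conditioned on something measured after the care that the intervention might alter. Part of the change could then be adjusted away, or the estimate distorted.

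**Working it through.** **1. Where each measure is used.**

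| Place | SDMC experience | PHQ-9 / GAD-7 |
|---|---|---|
| Abstract: informs success | yes | yes, as psychosocial well-being |
| Quantitative methods: collected pre and post | yes | yes |
| Table 1: basis for judging success | one row | no row |
| Data analysis: modelled outcome | yes | not named |
| Covariates: adjustment variable | not applicable | yes, as anxiety or depression |

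Table 1 has 3 input rows, 2 intermediate, 3 implementation and 1 service outcome, so 9 in all. The single service row is the only woman-level survey measure. Linking the Abstract's well-being to PHQ-9 and GAD-7 is an inference, but these are the only quantitative psychosocial measures described for women.

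**2. The plan's own sample size.** It was set for the mistreatment score, and the point above does not depend on it. It is needed only to gauge precision. Inputs (Sample size calculation): difference 2.5, SD 6, power 90%, 5% level, design effect 2, loss 10%.

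- Two-sided: n = 2 × [6 × (1.960 + 1.282) / 2.5]² ≈ 121.05, so 122 per group. Times 2 = 244; divided by 0.9 = 272 per group, and 488 / 0.9 gives 543 in total.
- One-sided: 99 per group. Times 2 = 198; divided by 0.9 = 220 per group, 440 in total.

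The stated 308 is not reproduced as a total or per group. Both readings are therefore carried forward.

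**3. Precision for a prevalence difference between rounds.** Assumptions: equal rounds; the 10% loss and design effect of 2 carry over from the mistreatment score; prevalence 29% to 66%, the range that Country context gives for women in Pakistan generally, with 50% as the widest case.

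Effective n per round = n × 0.9 / 2. Half-width = 1.96 × √[2p(1 − p) / effective n].

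| Reading of 308 | Effective n per round | p = 0.29 | p = 0.50 | p = 0.66 |
|---|---|---|---|---|
| Total (154 per round) | 69.3 | 15.1 points | 16.6 points | 15.8 points |
| Per round | 138.6 | 10.7 points | 11.8 points | 11.2 points |

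For mean PHQ-9 or GAD-7 the same calculation needs a standard deviation, which the article does not give.

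**The case against.** **Table 1 lists key indicators only, and an article leaves secondary analyses to a fuller document.** This is fair for a measure that is merely unlisted. It does not answer the conflict here: the Abstract gives well-being a part in judging success, and the section that fixes the basis for success points to a table without it. An analysis plan could add the comparison, but the article would still disagree with itself.

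**Anxiety and depression are legitimate confounders.** The Introduction names them among vulnerabilities that predispose women to discriminatory care, so a measure reflecting the woman's state before the birth would be a sensible covariate. The article names no such measure; the only ones it names are postpartum.

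**The study does not claim effectiveness.** The Discussion says it will not give robust evidence of effectiveness and that change in women's experiences is not the primary objective. That stands, and it limits the consequences. It applies equally to the experience score, which still has an indicator row and a regression.

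A reader might also infer three stronger things that the document does not support:

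- *That the psychological risk is never assessed.* It is: both scales are in the pre-post assessments. What is missing is their evaluation as outcomes. The Introduction, moreover, describes harm from poor care in general, not a risk of this intervention.
- *That the study would declare success on the experience score alone.* That score is one of nine rows, and the Covariates section also has feasibility, penetration and challenges inform success.
- *That the 42-day outcome period conflicts with the six-week home visit.* Six weeks is 42 days, and the 42 days can be read as the postpartum period of interest, not a visit deadline.

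**Conclusion.** The point holds as an internal inconsistency. Depression and anxiety are measured in both rounds, and psychosocial well-being is said to inform success. But they are absent from the indicators on which success is judged, are not named as modelled outcomes, and are analysed only as a covariate. This rests on reading the Abstract's well-being as PHQ-9 and GAD-7.

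The over-adjustment part is conditional: it applies if the covariate is the postpartum score.

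The achievable precision supports description, not a test of effect: about ±15 to 17 percentage points if 308 is the total and ±11 to 12 if it is per round. These figures concern prevalence, and depend on a design effect stated for a different outcome and on a prevalence range that is not specific to postpartum women at these facilities. They could reveal a large shift in either direction, but not a modest one.

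**What to change.** Reconcile the Abstract, Quantitative methods, Data analysis, Covariates and Table 1 so that depression and anxiety have one stated role:

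1. Add two service-outcome rows to Table 1, for PHQ-9 and GAD-7, at baseline and endline.
2. Name both in Data analysis as pre-post outcomes, reported descriptively as differences with 95% confidence intervals that allow for clustering by facility.
3. Remove postpartum PHQ-9 and GAD-7 from the covariates of the SDMC experience model. If a different measure of anxiety or depression was meant, say which and when it is taken.

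The cost is two table rows, two further comparisons on data already planned and one edit to the covariate list. No extra data collection is needed. The downside is wide intervals, so the text should say that these results are descriptive.
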